#### Participants

Participants in the *Nurturing Moms* study will be recruited through various channels: clinical/health settings, community outreach recruitment events and community organizations, Research Match, and UMiamiHealthResearch.org. Participants will undergo a screening process in which they must meet the following inclusion criteria: 18 years old or older, speaks and understands English, Black or Latina. Additionally, they must be pregnant (less than 36 weeks) or postpartum (up to 12 months after birth). Participants will be disqualified from inclusion in the study based on the following exclusion criteria: a diagnosis of psychosis, inability to speak or understand English, or being neither pregnant (>36 weeks) nor postpartum (up to 12 months). Individuals with a history of seizures, vertigo, significant vision or hearing impairment, significant motion sickness, epilepsy, or sensitivity to flashing light/motion are also excluded from participation. Injuries to the eyes, face, neck, or arms that would make the use of the hardware uncomfortable are also grounds for exclusion. The implementation of these criteria enhances internal validity, optimizing the relevance and reliability of research findings. We aim to enroll 50 participants (25 expectant and 25 postpartum).

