#### Statistical analysis plan

For the primary objective, General Linear Model procedures will be used to examine effects of Virtual Reality (VR) on stress over time among pregnant and postpartum moms. For the secondary objective, the User Experience Questionnaire and the Virtual Reality Neuroscience Questionnaire will be used to determine feasibility, usability, and acceptability of NurtureVR as an intervention. Measures of central tendency, and frequency distributions will be used for categorical data.

The main dependent measures will be continuous factors: maternal and pregnancy mental health and sleep scores (see **Table 1** for measures). Regression analysis will be used to explore whether sociodemographic factors (e.g., age, income, education), pregnancy factors (maternal experience scale) and postpartum factors (maternal experience scale and childbirth experience questionnaire) are associated with adverse mental and sleep health outcomes. In the statistical analysis, missing data will be handled using multiple imputation techniques to minimize bias and maintain the integrity of the analysis. Outliers will be identified through visual inspections of data distributions and statistical tests, and decisions about their inclusion will be based on their potential impact on the results and the underlying reasons for their occurrence. We will use sensitivity analyses to assess the robustness of findings. Adjustments for multiple comparisons will be made using the Bonferroni correction or false discovery rate (FDR) control to reduce the risk of Type I errors due to the number of outcomes being measured. Covariates such as age, parity (number of previous births), socioeconomic status, and baseline mental health status will be included in regression models to adjust for potential confounding factors and to provide a clearer understanding of the relationships between the intervention and outcomes. Only factors that show significant correlations in preliminary analysis will be entered in the final model. These data are significant as they will be used to generate effect size estimates (and sample sizes) for planned large-scale studies and to build preliminary exploratory models ascertaining factors that predict mental and sleep health outcomes among Black and Latina pregnant and postpartum women.

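### The covariate rule contradicts itself and screens on significance, and outlier inclusion turns partly on impact on the results; the harm falls mainly on the predictor regressions and, in the worst case, on the pre-post test

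*Protocol article*

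**What the plan says.** All the wording is in the protocol article, section Statistical analysis plan, apart from the sample size.

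- **Primary analysis:** "General Linear Model procedures will be used to examine effects of Virtual Reality (VR) on stress over time".
- **Adjustment:** "Covariates such as age, parity (number of previous births), socioeconomic status, and baseline mental health status will be included in regression models", with control of confounding given as the reason.
- **Selection, in the next sentence:** "Only factors that show significant correlations in preliminary analysis will be entered in the final model". The article gives neither a significance threshold nor a closed list of candidates.
- **Outlier detection:** "Outliers will be identified through visual inspections of data distributions and statistical tests".
- **Outlier handling:** "decisions about their inclusion will be based on their potential impact on the results and the underlying reasons for their occurrence".
- **Safeguard:** "We will use sensitivity analyses to assess the robustness of findings".
- **Use of the results:** the data are to be "used to generate effect size estimates (and sample sizes) for planned large-scale studies" and to build exploratory models of mental and sleep health outcomes.
- **Sample size** (section Participants): "We aim to enroll 50 participants (25 expectant and 25 postpartum").

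**The concern.** **The covariate rule.** The two adjacent sentences cannot both be followed when a named confounder is not significant in the screen. An analyst who follows the second sentence lets the data choose the model and then reports p-values and intervals as if it had been fixed in advance. In a sample of 50, such a screen tends to lose weak but real factors, admit chance ones, and overstate whatever it keeps. The overstated coefficients may then feed the planning of later studies.

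**The outlier rule.** Two criteria are given. The reason for an outlier, such as a recording error, is a sound ground. Its impact on the results is not, because the analysed sample can then depend on the answer. This rule reaches the primary pre-post comparison, where the covariate screen barely does.

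Both rules are written into the article. They are not details left to a fuller plan.

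**Working it through.** **The plan's own figure.** The article gives no figure for either rule. Its one planning figure is a required sample of 45 (df 44), in the Discussion, from a one-sample t-test with effect size 0.5, 95% power and alpha 0.05. It reproduces with a one-sided alpha (n = 45, power 95.1%); a two-sided alpha needs 54. That calculation contains no covariates, so this point does not change it.

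**Inputs.** From the article: n = 50 and the two rules. Assumed, because not stated: screen at two-sided p<0.05; independent normal candidates; 10 candidates, 9 null and one with correlation 0.20; outlier cut-offs of 2, 2.5 and 3 SD. The section names about eight overlapping candidates: age, income, education, parity, socioeconomic status, baseline mental health, the maternal experience scale and the childbirth questionnaire.

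**Step 1: chance entries.** P(at least one null factor passes) = 1 − 0.95^m.

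| Null candidates m | Probability |
|---|---|
| 4 | 18.5% |
| 8 | 33.7% |
| 9 | 37.0% |
| 12 | 46.0% |

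Simulation with 9 null factors gives 36-37%. A null factor is still significant in the final model in 32-33% of studies.

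**Step 2: overstatement.** At n = 50 the critical t on 48 df is 2.011. A factor therefore passes only if |r| ≥ 2.011/√(2.011² + 48) = 0.279. A true correlation of 0.20 cannot pass without being overstated at the screen. By simulation it is retained in about 29% of studies and then averages about 0.35, or 0.35/0.20 ≈ 1.7 times too large.

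**Step 3: intervals.** With 4 to 12 candidates, all null, a factor that passes is significant in the final model 86-95% of the time. Its nominal 95% interval covers the true value 5-15% of the time.

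**Step 4: consequence for planning, if such a coefficient were used.** For a correlation at 80% power and two-sided 5%, n = ((1.960 + 0.842)/atanh r)² + 3. With r = 0.20, n = 194. With r = 0.35, n = 62.

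**Step 5: effect of screening on the pre-post change.** With centred candidates, screening gives a type I error for the mean change of 5.0-6.2% across the settings run. With a true standardized change of 0.5, the mean estimate is 0.53 screened against 0.51 unadjusted. The effect is small.

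**Step 6: outliers.** Null mean change, n = 50, two-sided 5% one-sample t-test, 20,000 runs per setting. The last column takes whichever is most favourable of keeping all points, dropping all flagged points, or dropping only the high or only the low ones.

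| Data | Cut-off | Keep all | Drop all flagged, whatever the result | Chosen by effect on the result |
|---|---|---|---|---|
| Normal | 2 SD | 4.8% | 10.4% | 14.7% |
| Normal | 2.5 SD | 5.1% | 7.0% | 7.7% |
| Normal | 3 SD | 4.9% | 5.4% | 5.5% |
| t, 4 df | 2 SD | 4.7% | 8.2% | 15.7% |
| t, 4 df | 2.5 SD | 4.6% | 7.0% | 9.6% |
| t, 4 df | 3 SD | 4.7% | 5.8% | 6.9% |

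A separate simulation gave about 12-13%, 7-10% and 5.5-7% at the three cut-offs. Part of the excess comes from trimming itself, since deleting flagged points shrinks the standard error even when the result plays no part. Under the null, the mean absolute standardized change rises from about 0.115 to between 0.12 and 0.20 when removal is chosen by result.

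**The case against.** Several objections carry weight.

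- **Reach of the screen.** A reader might infer that all p-values, intervals and effect sizes in the study are biased by it. Step 5 does not support that. The predictor work is described as exploratory, and the effect sizes carried forward could be the pre-post changes. This stands and limits the point.
- **The outlier rule has a second limb.** A reader might infer that outliers are kept or dropped by impact alone. The article also names the reasons for their occurrence. Impact could mean leverage, not direction or significance. Step 6 is therefore a worst case and not the written rule. Even so, impact on the results remains a stated ground for inclusion, and nothing in the article confines it to a harmless meaning.
- **The cut-off matters.** At 2 SD, 96% of clean normal samples of 50 contain a flagged point; at 3 SD only 8-9% do, and the inflation nearly vanishes. This stands, so a range is needed.
- **Strong covariates survive.** A correlation of 0.5 passes the screen about 96% of the time. This also stands; the loss falls on weaker factors.
- **The contradiction may be loose wording.** The selection sentence might apply only to the exploratory factors, or the named covariates might be only the candidate pool. Either is possible, but the text does not say so, and the two readings give different models.
- **Sensitivity analyses are promised.** Their content may properly sit in a fuller plan, so one cannot say that they would fail. They would still surround a main analysis whose model and sample the data had helped to choose. The multiplicity adjustment is tied to the number of outcomes and does not cover either choice.

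**Conclusion.** The point holds in a limited form and should be acted on. The two covariate sentences conflict. Significance screening at n = 50 gives unreliable predictor estimates: about a 36% chance of admitting at least one null factor, and a true 0.20 retained in about 29% of studies and averaging about 0.35. These figures rest on assumed candidates (10 independent, 9 null), an assumed correlation and p<0.05 entry. With 4 to 12 null candidates the chance of a false entry runs from 18.5% to 46.0%.

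The documents do not support a claim that screening undermines the primary stress comparison, where type I error stays at about 5-6%. The outlier criterion can affect that comparison: about 5.5% to 15% in the worst case for normal data, slightly higher with heavier tails, near nominal at a 3 SD cut-off and 12-15% at 2 SD. Whether overstated predictor coefficients would enter later sample sizes is possible but not certain from the text.

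**What to change.** **Covariates.** Delete the screening sentence. Keep in the regression models the confounders that the protocol already names (age, parity, socioeconomic status, baseline mental health) plus cohort (expectant or postpartum), whatever their p-values. Where the pre-post change is estimated, centre them or use change as the outcome, so that the time effect keeps its meaning as an average change. Report all other factors as unselected exploratory estimates with intervals.

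**Outliers.** Delete impact on the results as an inclusion criterion. Keep all plausible values in the main analysis. Correct or remove only verified data errors, decided without regard to the result. Make a robust or outlier-excluded analysis one of the sensitivity analyses already promised. A robust one is preferable, because Step 6 shows that plain deletion at a tight cut-off inflates type I error by itself.

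**Cost.** A few sentences, no added data collection, and no change to the stated sample size calculation. About four to five degrees of freedom out of 50 go to covariates, some of them weak; categorical coding of socioeconomic status would use more.

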## Methods

### Study design overview

*Nurturing Moms* is a pre-and post-design study aimed at reducing stress among expectant and postpartum Black and Latina women through a 5-week exposure to NurtureVR, a virtual reality based digital therapeutic. NurtureVR is a digital maternal mental health and educational program combining mindfulness techniques, relaxation, and virtual reality-guided imagery of pregnant and postpartum experiences. The study was designed to address pregnant women and postpartum mothers experiencing serious psychological symptoms, specifically in the Black and Latina population where mental distress rates are disproportionately higher compared to the general population. Advanced digital solutions can be leveraged to provide quality maternal mental health care that is effective and accessible to all.

The study is driven by three objectives: 1) to assess whether NurtureVR reduces stress levels and mental health symptoms of pregnant and postpartum Black and Latina women; 2) evaluate whether NurtureVR improves sleep, as well as pregnancy and childbirth experiences; and 3) investigate whether NurtureVR improve pregnancy/postpartum health literacy.

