The sample size was chosen with a focus on the feasibility goals of this study, while also considering its potential for generating statistically significant results. We conducted a power calculation using G*Power 3.1 to assess whether our sample size could detect meaningful changes in key outcomes. Specifically, we used a t-test to identify means: difference from a constant (one-sample case), assuming an effect size of 0.5, a power of 95%, and an alpha error probability of 0.05. This analysis yielded degrees of freedom (Df) = 44 and a required total sample size of 45. These results suggest that our planned sample size of 50 participants is sufficient to detect significant findings in this exploratory study. While the primary aim is to assess feasibility and acceptability, this sample size ensures that we have enough statistical power to observe meaningful changes in stress levels and mental health symptoms, providing valuable insights to guide future research and larger-scale trials.

The absence of a control group is another limitation that may impact the internal validity of our findings, as it makes it challenging to attribute observed changes in stress and mental health symptoms solely to the VR intervention. The decision to forgo a control group was influenced by ethical considerations, as we aim to ensure that all participants benefit from the intervention, especially given the known disparities in access to maternal mental health support among Black and Latina mothers. To address this limitation, we plan to explore the use of historical controls from similar populations in previous studies and to conduct a randomized controlled trial (RCT) in the future to better isolate the effects of NurtureVR. This future RCT would allow for more robust comparisons and a deeper understanding of the intervention’s efficacy.

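### An uncontrolled pre-post change in about 50 women is to supply effect sizes and sample sizes for larger studies, but it does not estimate a between-arm treatment effect

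*Protocol article*

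**What the plan says.** All places are in the protocol article.

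- **Use of the data.** The Statistical analysis plan section closes by saying why the data matter: "they will be used to generate effect size estimates (and sample sizes) for planned large-scale studies". The same sentence adds exploratory models of factors that predict mental and sleep health.
- **Design.** Under Study design overview, the trial "is a pre-and post-design study aimed at reducing stress among expectant and postpartum Black and Latina women". Participants gives a target of 50 women, 25 expectant and 25 postpartum. The Discussion confirms that there is no comparator: "The absence of a control group is another limitation that may impact the internal validity of our findings".
- **Primary analysis.** "General Linear Model procedures will be used to examine effects of Virtual Reality (VR) on stress over time among pregnant and postpartum moms". No comparator term is possible.
- **Attribution.** The Discussion says of the missing control group that "it makes it challenging to attribute observed changes in stress and mental health symptoms solely to the VR intervention". It then says that historical controls will be explored and that a randomised trial will follow.
- **Effect-size scale.** The only effect size defined is in the trial's own power calculation in the Discussion: "we used a t-test to identify means: difference from a constant (one-sample case"), with effect size 0.5, power 95%, alpha 0.05 and a required sample of 45.

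**The concern.** A later two-arm trial is sized on the difference between arms at follow-up, usually divided by the SD of the outcome. This pilot cannot observe that difference. It observes how far the same women move between baseline and follow-up, and part of that movement would have happened without the programme.

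Timing makes this more than a formality. Women enter before 36 weeks of pregnancy or up to 12 months after birth (Participants). Under Timeline, headsets ship one week after baseline, the programme runs five weeks and the surveys are repeated three months later. Follow-up is therefore about 1 + 5 + 13 = 19 weeks after baseline. With a 40-week term (assumed), a woman enrolled after about 21 weeks would normally have given birth in between. Delivery, recovery, time since birth, regression to the mean and answering the same scale twice are all inside the change. The covariates listed in the plan cannot remove them without a comparator.

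What is at stake is the size of the next trial. If the change is carried forward as a planning effect, that trial inherits a bias of unknown size and sign, together with the imprecision of about 50 women.

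**Working it through.** **1. The plan's own figure.** Inputs (Discussion): one-sample t-test, effect size d = 0.5, power 95%, alpha 0.05. Power is the upper tail, beyond the critical t value, of a noncentral t with n − 1 degrees of freedom and noncentrality d√n.
- One-sided: n = 44 gives 94.7% and n = 45 gives 95.1%. The stated 45 (df = 44) is reproduced.
- Two-sided: n = 54 is needed, and n = 50 gives 93.4%.

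This calculation powers detection of any mean change, whatever its cause. In it, d is mean change divided by the SD of change (written dz below).

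**2. Precision of the change.** Assume an observed dz of 0.5 (the plan's own planning value) and all 50 women analysed. Then t = 0.5 × √50 = 3.54. The 95% limits are the values δ for which a noncentral t (49 df, noncentrality δ√50) puts 2.5% above, or 2.5% below, 3.54. The result is **0.20 to 0.79** (0.203 to 0.792).

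**3. What that implies for a later trial.** Read each value as a between-arm d in a two-sample t-test, two-sided 5%, 90% power, with noncentrality d√(n/2) and 2n − 2 df:

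| d | n per arm |
|---|---|
| 0.203 | 509 |
| 0.5 | 86 |
| 0.792 | 35 |

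Sampling error alone spans roughly a 15-fold range (509/35 = 14.5).

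**4. Effect of a non-programme component.** Suppose the trial is sized on 0.5 (86 per arm), but part of the 0.5 is background change. The sizes are assumed, because the document gives none.

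| Not due to programme (SD units) | Share of change | True d | Power at 86 per arm |
|---|---|---|---|
| 0.1 | 20% | 0.4 | 74% |
| 0.2 | 40% | 0.3 | 50% |
| 0.3 | 60% | 0.2 | 26% |

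If background stress instead rose by 0.1 SD units, the true d would be 0.5 + 0.1 = 0.6 and power 97%. The trial would then be larger than needed.

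**5. Scale.** If the pilot's effect is standardised by the SD of change, then with equal SDs and pre-post correlation r, d = dz × √(2(1 − r)). For dz = 0.5 (r assumed, 90% power):

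| r | d on outcome-SD scale | n per arm |
|---|---|---|
| 0.3 | 0.59 | 62 |
| 0.5 | 0.50 | 86 |
| 0.7 | 0.39 | 142 |
| 0.85 | 0.27 | 282 |

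The two scales agree only at r = 0.5. The article gives no correlation.

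**The case against.** The strongest reply is that the sentence looks ahead and changes nothing in this trial's conduct. It refers to large-scale studies without specifying a randomised trial, and it does not say that a raw pre-post change will be inserted as a between-arm effect. The effect sizes could include associations from the regression models, and the sizing method can be settled in the later protocol. The authors disclose the missing control group and mention historical controls and a randomised trial.

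Part of this stands. The conversion method is detail that an article may omit, and standardisation by the SD of change is an inference from the power calculation. What remains is that the data are assigned to effect-size and sample-size estimation, the Discussion names a randomised trial as a next study, and the design offers no other intervention effect. Historical controls are only to be explored, with no source, method or link to the planning effect.

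A reader might also infer more than the documents support:

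- **That the bias is upward and the next trial would be underpowered.** This is not shown. No minimum stress score is required at entry, so the usual driver of regression to the mean is absent, and the article does not say whether stress rises or falls after delivery. The scale mismatch also works in both directions.
- **That the authors concede the change cannot be attributed to the programme.** They say only that attributing it solely to the programme is challenging.
- **That effect sizes are the pilot's main output.** Predictor models, feasibility, acceptability and user feedback are also stated outputs.
- **That 0.1, 0.2 and 0.3 are fractions of the change.** They are SD units. Losing 10%, 20% or 30% of the change (d = 0.45, 0.40, 0.35) would leave power of about 84%, 74% and 63%.

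**Conclusion.** The point holds as a wrong planned use of the data, not as a failure to disclose. One stated use of the pilot is to derive planning effects and sample sizes, and the only intervention effect it can yield does not separate the programme from everything else that happens over the interval. The Discussion's caveat needs to govern the sentence in the Statistical analysis plan section, and at present it does not.

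The illustration shows that the issue is material: at the plan's own value of 0.5, sampling error and a modest background change can each alter the required size, or the power, of the next trial several-fold or by tens of percentage points. The figures rest on an assumed observed change of 0.5, full retention of 50 women, and assumed background changes and correlations. The article gives no SD, correlation or dropout rate. The direction of the bias is open. The point warrants a change to the text, but does not affect data collection or the primary analysis.

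**What to change.** Revise the closing sentence of the Statistical analysis plan section to state three things:

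1. The pre-post change will be reported with its confidence interval as a descriptive result and will not be used as the between-arm planning effect.
2. The pilot will supply planning parameters with confidence intervals, separately for the expectant and postpartum cohorts: SD of the Perceived Stress Scale, baseline-to-3-month correlation, retention, adherence and recruitment rate. Table 2 already schedules the scale at baseline and three months, and the administrative control panel records module use.
3. The later trial will be sized on a prespecified important between-arm difference, combined with those parameters. A conservative (upper-limit) SD is a sensible choice, since each cohort has only about 25 women.

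If historical controls are to play any part in planning, the source and method should be named.

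The cost is a reworded sentence, a few extra summary statistics and a less ambitious claim. No procedure, visit or instrument changes.
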